# Stainless steel versus titanium volar multi-axial locking plates for fixation of distal radius fractures: a randomised clinical trial

**DOI:** 10.1186/1471-2474-15-74

**Published:** 2014-03-11

**Keywords:** Distal radius, Randomized trial, Volar plating, Trimed, Medartis, Wrist, Surgery

## Abstract

**Background:**

Distal radius fractures are among the most common fractures seen in the hospital emergency department. Of these, over 40% are considered unstable and require some form of fixation. In recent years with the advent of low profile plating, open reduction and internal fixation (ORIF) using volar plates has become the surgical treatment of choice in many hospitals. However, it is currently unknown which plating system has the lowest complication rate and/or superior clinical and radiological outcomes following surgery. Few studies have compared different types of plates, which may have various features, different plate and screw designs or may be manufactured from different materials (for example, stainless steel or titanium). This study will specifically investigate and compare the clinical and radiological outcomes and complication rates of two commonly used volar plating systems for fixation of distal radius fractures: one made from stainless steel (Trimed™ Volar Plate, Trimed™, California, USA) and the other made from titanium (Medartis® Aptus Volar Plate, Medartis®, Basel, Switzerland). The primary aim of this study is to determine if there is a difference on the Patient Reported Wrist Evaluation six months following ORIF using a volar plate for adult patients with a distal radius fracture.

**Methods/Design:**

This study will implement a randomized prospective clinical trial study design evaluating the outcomes of two different types of volar plates: one plate manufactured from stainless steel (Trimed™ Volar Plate) and one plate manufactured from titanium (Medartis® Aptus Volar Plate). The surgery will be performed at a major trauma hospital in Brisbane, Australia. Outcome measures including function, adverse events, range of movement, strength, disability, radiological findings and health-related quality of life will be collected at 6 weeks, 3, 6, 12 and 24 months following surgery. A parallel economic analysis will also be performed. This randomized clinical trial is due to deliver results in December 2016.

**Discussion:**

Results from this trial will contribute to the evidence on operative management of distal radius fractures and plate material type.

**Trial registration:**

ACTRN12612000969864

## Background

Distal radius fractures are the most common type of all fractures seen in the emergency department and constitute 10% to 25% of all extremity fractures [1,2]. The incidence of distal radius fractures continues to rise as the population in industrialised countries grows in line with an increase in age and life expectancies [3,4]. The occurrence of distal radius fractures peaks within two different age groups: high energy trauma, typically in males aged 5–24 years, or low-energy injuries commonly seen in the elderly female population aged 65 years and older [5].

The treatment of distal radius fractures has developed greatly over recent years with a move towards treating these fractures by means of internal fixation. Although closed reduction and casting remain viable options for some non-displaced simple fractures of the distal radius, the role of ORIF continues to grow due to its ability to more reliably restore wrist anatomy, minimize immobilization and establish acceptable clinical outcomes [4]. Numerous methods of surgical stabilisation exist including: manipulation with Kirschner wires (k-wires), external fixators, dorsal and volar plating and fragment specific fixation. All have been found to be successful in maintaining correction of the reduced fracture however volar plating has more recently become the favourable choice for managing distal radius fractures especially in more complex fracture patterns and/or osteoporotic bone [6-8]. The advent of variable angle volar plating systems has also allowed cases with increasing comminution and displacement, poor bone quality, and dorsally angulated fractures, to be fixed with less tendon irritation and the reduced need for hardware removal [8,9]. In addition, volar plating allows restoration of anatomy, stable fixation, reduced periods of immobilisation and earlier return to function [6,8]. As the popularity of volar plating has increased so has the number and type of volar plating systems available to orthopaedic surgeons. Differences range from the plate design (i.e. shape and contour), material, type, locking screw mechanism and number of screws used. The general benefits of variable angle plating systems have been reported to include [8]:

•Flexible deployment with respect to variations in radial size;

•Accommodation of proximal/distal variation in volar fracture lines;

•Accommodation of medial and lateral variation in fracture lines;

•Adaptation of screw direction to specific fracture fragments.

A recent literature review conducted by Gehrmann et al. on distal radius fracture management in the elderly, found that patients with higher demands benefit from fracture stabilisation using locking volar plates [3]. Volar plating with fixed-angle screws may also be particularly suitable for elderly patients whose fractures take longer to heal or are more susceptible to pin-site infection.

Additionally, newer features of volar plates, such as locking and variable angle mechanisms, have been thought to further reduce complication rates and improve effectiveness in patients of all ages [6]. This remains controversial however, as a number of complications including loss of fixation, tendon irritation or rupture, median nerve complications and distal radial ulnar joint dysfunction, have been reported in the literature [10,11]. Various factors, such as plate and screw type, have been found to contribute to this complication rate, which highlights the importance of investigation into clinical and radiological outcomes of surgery for this patient population.

Comparison of complications between dorsal and volar plates has been examined previously with results indicating a higher rate of association between volar plates and neuropathic complications but less tendon irritation or ruptures than dorsal plates [2]. A study by Soong et al. also found that very few complications were recorded in their cohort of distal radius fractures fixed with volar plates, compared with dorsal plates [11].

A retrospective study of 115 patients with comminuted intra-articular distal radius fractures was performed by Richards et al. who compared radiographic and clinical outcomes of patients treated with external fixation to those treated with volar plate internal fixation [10]. They reported fewer complications, better range of movement, pain and functional scores in the ORIF group.

A randomised clinical trial of 53 patients comparing external fixation and ORIF (either dorsal or volar plates) by Grewal and colleagues found that ORIF had significantly lower Patient Rated Wrist Evaluation (PRWE) scores across all time points (3, 6, 12 months) with better outcomes observed in the volar plating group [12].

Park et al. investigated the clinical outcomes of a consecutive cohort of 20 patients undergoing ORIF of their distal radius fractures using the Medartis Aptus Volar Plate up to a one year period [4]. They found that all fractures healed in every case by 12 weeks post-operation with no loss of reduction in 19 cases (of 20 patients). Range of movement, grip strength and Disability of the Arm, Shoulder and Hand (DASH) scores were all within acceptable ranges.

Previous studies have investigated the clinical and radiological outcomes of volar plating systems in cohort series designs [9,13,14]. Osada et al. found in their series of 49 fractures in 49 patients fixed with volar plates, good radiological results, good to excellent Gartland and Werley scores, low DASH scores, a high degree of patient satisfaction and no record of complications except plate removal [13]. A total of three plates were removed between six and 10 months postoperatively. Two plates were removed due to patient request and the other was removed because the distal locking pins appeared to be intra-articular on the computed tomography scan [9]. Sanchez-Crespo retrospectively reviewed 145 patients (fixed with either a Medartis Aptus Volar 2.5 mm Plate or Synthes 2.4mmLCP distal radius plate) and analysed results of 95 of these patients [14]. They found good mean functional scores using the PRWE (mean 13; range 0–64) however 8% of patients presented with a complication (e.g. chronic pain, malunion, tendon tears, carpal tunnel syndrome, or requiring hardware removal).

Titanium and stainless steel volar plating systems for distal radius fractures are both readily available and in common use in orthopaedic surgery. Titanium implants have been reported to have benefits including reduced implant stiffness, increased biocompatibility and diminished stress shielding [15]. However tenosynovitis and extensor tendon ruptures have been reported in the use of low profile titanium plates used for dorsal fixation of distal radius fractures [16]. Conversely, stainless steel plates have been thought to have less tendon irritation and adhesions when used in wrist surgery [16].

Recently, Souer et al. specifically investigated the clinical and radiological outcomes comparing 2.4 mm titanium and 3.5 mm stainless steel volar plates and found improved range of movement in the group that received the 2.4 mm titanium plate at 12 and 24 months post-surgery [13]. However, patients in the 3.5 mm stainless steel volar plate group had better radiological outcomes at all time points. Along with the obvious limitations in the study design (retrospective review of a prospective cohort), sample size (n = 62), and high loss to follow-up, the results could be attributed to either the plate thickness or material type. To date, no randomized trials are known to exist comparing material type (i.e. stainless steel versus titianium) of volar plates.

The research question for this study is: Do patients who have their distal radius fractures internally fixated with a titanium plate have the same outcomes as patients who have their distal radius fractures internally fixated with a stainless steel plate?

## Methods/Design

### Design

This is a prospective double blind randomized clinical trial. This study was approved by the Metro South Human Research Ethics Committee (Ref: HREC/12/QPAH/293) and registered with the Australian New Zealand Clinical Trials Registry (ANZCTR) (Ref: ACTRN12612000969864).

### Study participants

Participants will be selected for inclusion in the study if:

1) Aged 18 years and over; male or female;

2) Acute (defined as surgery needs to take place within 3 weeks of injury) distal radius fracture as diagnosed on x-ray and/or CT scan with surgical fixation.

Participants will be excluded from the study if they present with a:

1) History of previous wrist fracture, injury or surgery in the same wrist with ongoing symptoms or functional limitation at the time of the distal radius fracture;

2) Significant acute associated trauma or injuries to the ipsilateral upper limb;

3) Associated significant other injuries increasing risk of surgery or preventing compliance with rehabilitation protocol (e.g. traumatic brain injury; spinal cord injury; traumatic upper extremity surgery);

4) Wrist fractures that are unable to be fixed adequately with only a volar plate (e.g. requires additional fixation). If this is determined intra-operatively, patients will not be progressed further into the study;

5) Medical/Anaesthetic contraindications to surgery;

6) Unable to comply with rehabilitation or attend follow up appointments as determined at the time of surgery (e.g. resides internationally);

7) Are currently pregnant.

### Trial interventions

The interventions being compared are:

Intervention A: Early surgical intervention using a Stainless Steel volar locking plate.

Intervention B: Early surgical intervention using a Titanium volar locking plate.

The hospital involved in the trial currently use both types of plate for open reduction and internal fixation of distal radius fractures and all of the surgeons involved are surgically experienced with volar plate fixation for distal radius fractures. The operative technique takes place under general anesthetic and each patient will undergo the surgery according to their random allocation of Intervention A or Intervention B. Randomisation will occur at the time of surgery booking after the patients has been appropriately consented and enrolled into the study.

All patients undergo general anaesthetic and high arm tourniquet control. The approach is via a volar incision and then through the bed of the flexor carpi radialis tendon. The plane between the flexor tendons and pronator quadratus is identified and pronator quadratus is then dissected carefully as a flap from the radial side to expose the underlying distal radius. Brachioradialis is released completely due to its adverse coronal plane deforming force upon the fracture.

Reduction of the fracture is dependent upon the fracture pattern and may be indirect with traction and manipulation, or direct with mobilization of the fragments directly with k-wires or bone punch. After the fracture has been initially temporarily stabilized with k-wires the volar multi-axial locking plate is applied and secured with screws to gain control of the radial and ulnar columns. It is paramount to ensure that the ulnar column is held securely to prevent any ulnar translocation. In the majority of cases the technique during surgery is to insert the variable angle distal row screws first according to the surgeons technique and to place them in the most appropriate subchondral configuration at the most appropriate depth whilst accommodating the variable fracture fragment configuration. The plate is reduced to the shaft and the diaphyseal screws are then inserted whilst fine-tuning fracture reduction [8]. If there is any significant bone loss the void is filled using calcium phosphate injectable bone substitute.

Most fractures are amenable to this single plate fixation, but some complex fractures require specific fragment plating techniques with additional metalwork insertion and if this is required intra-operatively then the patient will be excluded and will not continue further in the study. Occasionally, patients require a small dorsal incision and arthrotomy to aid the fracture reduction and as long as this is only for reduction purposes they may remain in the study.

Closure of the wound begins initially with suturing of pronator quadratus back to its original position where possible. In the majority of cases, even when the pronator quadratus is lacerated by the fracture there will be sufficient tissue available for repair to cover the most distal aspect of the plate. This soft tissue layer can prevent flexor tendon irritation on the distal plate. Subcuticular and skin suturing technique is down to the surgeon’s preference. The wound is dressed with a waterproof dressing and then a bulky dressing in neutral position is applied to the wrist, allowing full range of movement of the fingers including metacarpal phalangeal joint flexion. The patient is given a sling for comfort and to elevate the hand [8].

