#### Outcome measures

A suite of outcome measures recommended and previously used in research for this patient group will be used [7,9,13]. A summary of these outcome measures and the tool used are detailed in Table 2.

**Table 2 T2:** Outcome measurement tools

**Outcome**	**Assessment**
Function	Patient rated wrist evaluation*
Disability	Disabilities of the arm, shoulder and hand
Health-related quality of life	EQ-5D-3 L (Australian)
Pain	Visual analogue scale
Satisfaction	Visual analogue scale
Grip strength	Jamar dynamometer
Range of movement	Goniometric evaluation
Radiological outcomes	Study specific generated checklist
Adverse events	Study specific generated checklist

*Primary outcome measure.

Patient demographic information and baseline (pre-injury) functional status will be collected after consent to take part in the trial. Structured information regarding other injuries which may affect outcome e.g. disruption of the carpal ligaments, will be collected but all patients will be included in the analysis.

The primary outcome measure for this study is the:

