#### Sample size

Recruitment of a total of 130 participants (65 in each group) is anticipated to take approximately 104 weeks (assuming a 75% recruitment rate of eligible participants) based on historical emergency department presentation rate of this patient group. After allowing for a 30% loss to follow up, this investigation has 95% power to detect a between group mean difference in the primary outcome function (PRWE) of 10 (SD-15).

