#### Randomisation

Patients providing written informed consent for participation in this trial will be randomly assigned to either early intervention group (titianium or stainless steel volar multi-axial locking plates). The randomisation sequence will be computer generated and concealed in sequentially numbered sealed, opaque envelopes by a person, not otherwise associated with this research, to eliminate any risk of randomisation/recruitment bias. Each envelope will contain a sheet of paper with the words either “TITANIUM” or “STAINLESS STEEL”. This randomisation process will occur at the time of surgery booking.

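### Patients are randomised at surgery booking but removed from the study if additional metalwork proves necessary in theatre, so the comparison of retained patients is no longer fully protected by randomisation

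*Protocol article*

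**What the plan says.** The protocol article fixes the order of events in four places.

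- **Allocation.** Trial interventions: "Randomisation will occur at the time of surgery booking after the patients has been appropriately consented and enrolled into the study". The Randomisation section repeats it: "This randomisation process will occur at the time of surgery booking". The envelope names the plate.
- **Knowledge of the arm.** Trial interventions: "each patient will undergo the surgery according to their random allocation of Intervention A or Intervention B". The surgeon implants the allocated plate and so must know which it is.
- **Exclusion in theatre.** Study participants, exclusion 4, covers fractures that a volar plate alone cannot fix adequately, and adds: "If this is determined intra-operatively, patients will not be progressed further into the study". Trial interventions says the same of additional metalwork: "if this is required intra-operatively then the patient will be excluded and will not continue further in the study".
- **Exclusion 6.** Study participants: "Unable to comply with rehabilitation or attend follow up appointments as determined at the time of surgery". The example given is living abroad. As worded, this is also judged after booking.

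The Sample size section plans 130 participants, 65 per group, allows for 30% loss to follow-up, and does not mention exclusions in theatre.

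**The concern.** Removing randomised patients is usually harmless if it rests on facts fixed before allocation and is judged without knowledge of the arm. Exclusion 4 as applied in theatre does not secure the second condition, and may not meet the first. The judgement that a volar plate alone is not enough can be made with the allocated plate in hand. The Background notes that plating systems differ in design, locking mechanism and screw number, so the threshold for adding metalwork could differ between the two systems.

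If it does, the arm that more often needs supplementary fixation loses more of its difficult fractures, and its retained patients look better on the PRWE at six months. Follow-up of the removed patients stops, so their outcomes cannot be recovered at the analysis stage. The number analysed may also fall below the number planned.

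**Working it through.** **1. Does any other text restore these patients?** Three places come near.

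- Outcome measures says that information on other injuries "will be collected but all patients will be included in the analysis". This concerns associated injuries such as carpal ligament disruption. It does not reverse the exclusion in theatre.
- Rehabilitation says that deviations will be documented and controlled for in the analysis. This sits under hand therapy and presupposes a patient who is still in the study.
- Statistical analysis offers a mixed model for missing values. Table 3 schedules the PRWE from 6 weeks onward, with no baseline measurement, so a patient removed in theatre contributes no PRWE value to that model.

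None of them does.

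**2. The plan's own power figure.** Inputs from the Sample size section: 65 per arm, 30% loss, difference 10, SD 15, stated power 95%. The article gives no alpha or sidedness; 5% is assumed.

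- Analysable patients per arm: 65 × 0.70 = 45.5.
- Standard error: 15 × √(2/45.5) = 3.14, so the standardised difference is 10/3.14 = 3.18.
- Two-sided t-test power: 88.2% (normal approximation 88.9%).
- One-sided t-test power: 93.5% (normal approximation 93.8%).

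The stated 95% is therefore approached after 30% loss only with a one-sided test. The right two-sided starting point for this issue is about 88%.

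**3. Cost in precision if the exclusions come on top of the 30%.** The exclusion rate is not in the article. Assume 10% in each arm.

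- Analysable patients per arm: 65 × 0.90 × 0.70 = 40.95, about 41.
- Two-sided t-test power: 84.7% at 41 per arm.
- Reduction: 88.2 − 84.7 = 3.5 percentage points.

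By the normal approximation, assumed exclusion of 5%, 10%, 15% and 20% takes two-sided power from 88.9% to 87.3%, 85.5%, 83.4% and 81.2%.

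**4. Bias.** Let a fraction p of an arm be excluded, and let excluded patients score D points worse than retained ones. The all-patient mean is (1 − p) × m + p × (m + D) = m + pD, where m is the retained mean, so m = all-patient mean − pD. With no true plate effect and the same D in both arms, bias = D × (pB − pA), favouring the arm with more exclusions. D and p are assumptions. The type I error uses a two-sided 5% normal test, SD 15 and 65 × (1 − p) × 0.70 patients per arm.

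| Exclusion, arm A v arm B | Bias, D = 10 | Bias, D = 20 | Type I error, D = 10 to 20 |
|---|---|---|---|
| 10% v 10% | 0 | 0 | 0.050 |
| 5% v 10% | 0.5 | 1.0 | 0.053 to 0.061 |
| 5% v 15% | 1.0 | 2.0 | 0.060 to 0.092 |
| 5% v 20% | 1.5 | 3.0 | 0.073 to 0.144 |

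Against the 10-point target difference, 0.5 to 3.0 points is 5% to 30%.

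**The case against.** The strongest reply is that the article ties extra metalwork to the fracture, not to the plate. Trial interventions says that some complex fractures need fragment-specific techniques and that most do not. Both devices are multi-axial locking plates, and the hospital already uses both. If exclusions are equal in rate and reason, there is no bias. This stands as a limit on size: the documents show that exclusion **can** depend on the plate, not that it does. It does not remove the problem, because the decision is made with the arm known and the plan keeps no outcome data that could show the exclusions to be harmless.

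Four stronger readings are tempting, and the documents do not support them.

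- *The exclusions are plate-dependent and break the comparison.* No rates by plate are given, and the two systems' ability to hold fragments is not compared. The supportable statement is that the comparison is no longer fully protected.
- *The operation also reveals who cannot comply.* Exclusion 6 is judged at surgery, but its example is a fact knowable beforehand, and nothing links it to the plate. It is a timing point only.
- *A key outcome disappears.* Need for supplementary fixation is neither in Table 2 nor in the adverse event list. The listed fixation failure is an implant not maintaining fixation, and it is still recorded for patients who continue.
- *The exclusions take power from 95% to 85%.* Most of that gap is already there after the 30% loss under a two-sided test. The article also does not say whether theatre exclusions fall inside the 30%.

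A further reply is that the research question compares the two plates and that adding patients with extra metalwork alters it. That is a fair reason to show the single-plate set as well. It is not a reason to let a post-allocation decision define the primary set.

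**Conclusion.** The concern holds in a limited form. The article commits the trial to removing randomised patients for a reason judged in theatre by a surgeon who knows the arm, with no further follow-up. A fuller analysis plan could not recover outcomes that were never collected.

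The direction is known: any difference in exclusion favours the arm with more of it. The size is not known. On the assumptions above it runs from zero, through 0.5 to 1.0 PRWE points for a 5-point gap in exclusion rates, to 1.5 to 3.0 points for a 15-point gap. The upper end needs 20% of one arm excluded, which is a strong assumption given that most fractures are said to suit a single plate. The loss of precision is secondary: about 3.5 percentage points of power for a further 10% loss, and only if those patients are not already counted in the 30%.

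**What to change.** - Keep every randomised patient on the existing follow-up schedule, including those given additional metalwork, and analyse them in the allocated arm in the primary analysis. Surgical care does not change.
- Report the number of patients with supplementary fixation, and the reasons, by arm.
- Show the single-plate-only set as a sensitivity analysis.
- As a minor point unrelated to the plate, assess exclusion 6 before allocation.

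Opening the envelope later, in theatre, is optional. It would shorten the interval between allocation and the decision, but would not by itself remove exclusions that arise after the plate is applied, so it does not replace the first step.

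The cost is a protocol amendment, follow-up of a few more patients, and a slightly more heterogeneous primary analysis set.
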